## 8.1.2 Serious Adverse Events

A serious adverse event is any untowards medical occurrence that, at any dose:

- - Results in death
  - Is life-threatening
  - Requires hospitalization or prolongation of existing hospitalization—i.e., the AE requires at least a 24-hour inpatient hospitalization or prolongs a hospitalization beyond the expected length of stay.

Hospitalization or prolongation of existing hospitalization for social reasons will not be reported as an SAE.

- - Results in disability/incapacity
  - Results in congenital anomalies/birth defects
  - Important medical events

Medical or scientific judgement should be exercised in deciding whether SAE reporting is appropriate in other situations. An important medical event is an event that may not result in death, be life-threatening, or require hospitalization but is clearly of major clinical importance. The AE may jeopardize the subject or require intervention to prevent a serious outcome.

## 8.2 Assessment of Severity

With the exception of hematologic AEs, all AEs will be graded according to the National Cancer Institute Common Toxicity Criteria version 5.0. When the National Cancer Institute Common Toxicity Criteria version 5.0 criteria do not apply, severity will be defined according to the following criteria:

| **Severity** | **Description** |
| --- | --- |
| Grade 1- Mild | Asymptomatic or mild symptoms; clinical or diagnostic observations only; intervention not indicated |
| Grade 2- Moderate | Minimal, local or noninvasive intervention indicated; limiting age-appropriate instrumental activities of daily living (ADL) |
| Grade 3- Severe | Medically significant but not immediately life threatening; hospitalization or prolongation of hospitalization indicated; disabling; limiting self-case ADL |
| Grade 4- Life-threatening | Life-threatening consequences; urgent intervention indicated |
| Grade 5- Death | Death |

## 8.3 Assessment of Causality

Investigators must determine the relationship between each AE or SAE and the study treatment. The relationship between an AE or SAE and the study treatment will be defined according to the following criteria:

- - Definite: There is a clear temporal relationship to the study treatment, with no other possible cause
  - Possible: A temporal relationship to the study treatment is not clear, and alternative aetiologies are possible
  - Not related: There is no temporal relationship to the study treatment, and/or there is evidence of an alternative cause, such as a concurrent medication or illness

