# 3. Study Design

This is a prospective single-arm clinical study to evaluate luspatercept for promoting hematopoietic recovery in patients with poor hematopoietic reconstitution after allo-HSCT.

Patients with poor hematopoietic reconstitution after HSCT receiving luspatercept treatment will be enrolled, and the dose of luspatercept ranged from 0.7 to 1.4 mg/kg subcutaneously on the basis of routine supportive therapy. The complete blood count will be monitored every 7 days within 20 days from the beginning of luspatercept treatment. The primary endpoint was defined as hematologic improvement-erythroid (HI-E), which included the achievement of red blood cell transfusion independence (RBC-TI) for patients requiring RBC transfusions before administration, as well as a mean Hb increase ≥ 1.5 g/dL for RBC-TI patients at the first administration. The secondary endpoints included proportions of patients who achieved absolute increases in neutrophil ≥ 0.5 × 10^9^/L and platelet counts ≥ 30 × 10^9^/L, respectively; proportions of patients who achieved HI-neutrophil (HI-N) and HI-platelet (HI-P) counts; measurements of white blood cell (WBC), absolute neutrophil and platelet counts; and mean changes from baseline.

All the subjects will be followed for safety and tolerability within 20 days post-treatment. With the exception of haematologic adverse effects (AEs), all AEs will be graded according to the National Cancer Institute Common Toxicity Criteria version 5.0.

AEs= adverse effects; allo-HSCT= allogeneic hematopoietic stem cell transplantation; BM= bone marrow; EC= endothelial cell; HI-E= hematologic improvement-erythroid; HI-N= hematologic improvement-neutrophil; HI-P= hematologic improvement-platelet; MDS= myelodysplastic neoplasm; RBC-TI= red blood cell transfusion independence; TGF-β1= transforming growth factor-beta 1; WBC= white blood cell.

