## 9.2. Premature Termination of the Study

Reasons for premature termination of the study include external events, repetition of SAEs, an increasing incidence of treatment-related death and slow study enrolment. All the subjects will be informed of the premature termination of the study via written consent. Any subject who decides to discontinue participation in the study must report to the principal investigator.

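### The causality categories in Protocol 8.3 leave gaps, overlap, and never allow an event with clear timing to be coded Possible

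*Protocol*

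**What the plan says.** Protocol 8.3 makes causality an event-by-event judgement: "Investigators must determine the relationship between each AE or SAE and the study treatment". It allows three answers.

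- The text for *Definite* reads "There is a clear temporal relationship to the study treatment, with no other possible cause", which sets two conditions.
- The text for *Possible* reads "A temporal relationship to the study treatment is not clear, and alternative aetiologies are possible", which again sets two.
- The text for *Not related* reads "There is no temporal relationship to the study treatment, and/or there is evidence of an alternative cause, such as a concurrent medication or illness", with the two limbs joined differently.

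Four other places bear on what these answers are used for.

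- Section 8.4 requires all AEs and SAEs to be recorded whatever their causality, and every SAE to go to the ethics committee within 24 hours. The SAE form must carry the investigator's assessment of relationship to treatment.
- Section 11.2.2.3 (Analysis of Safety) plans to summarise the incidence and severity of AEs, without restricting this to related events.
- Section 9.2 lists "an increasing incidence of treatment-related death" among the reasons for ending the study early.
- Section 3 describes a single-arm study in patients after allogeneic transplantation, with luspatercept given "subcutaneously on the basis of routine supportive therapy". Section 2.1 places safety in the primary objective.

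**The concern.** A causality scale should give each event exactly one place, and a closer time link to the drug should never make a drug attribution harder. The definitions in 8.3 appear to fail on both counts. *Definite* is closed as soon as another cause is possible. The only intermediate category demands that timing be unclear. *Not related* can be reached on either of two limbs, one of which ignores timing. An event that closely follows an injection and also has a competing explanation has no route to *Possible*.

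With no control arm to separate drug effects from background, the investigator's causality call is the only attribution made for each event. It goes to the ethics committee on the SAE form. It is also the only relatedness classification the protocol supplies for reading treatment-related death in 9.2. An analysis plan could not repair this, because investigators assign the category under 8.3 and the analysis can only tabulate what they entered.

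**Working it through.** There is no stated figure to reproduce and no rate, error level or sample size is involved. The check is a cross-tabulation of the three definitions.

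**Inputs, all from 8.3.** Timing has three levels in the text: clear (*Definite*), not clear (*Possible*), none (*Not related*). Alternative cause also has three: no other possible cause (*Definite*), an alternative that is possible (*Possible*), and evidence of an alternative (*Not related*). An alternative for which there is evidence is taken to be possible as well.

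**Rules applied.**
- *Definite* = timing clear AND no possible alternative.
- *Possible* = timing not clear AND an alternative possible.
- *Not related* = no temporal relationship OR evidence of an alternative. The and/or makes either limb sufficient.

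| Timing | No alternative | Alternative merely possible | Evidence of an alternative |
|---|---|---|---|
| Clear | Definite | no category | Not related |
| Not clear | no category | Possible | Possible and Not related |
| None | Not related | Not related | Not related |

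**Count.** Definite 1, Possible only 1, Not related only 4, two categories at once 1, no category 2; 1 + 1 + 4 + 1 + 2 = 9.

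**Reading the table.**
1. *Top row.* With clear timing the outcomes are Definite, nothing, or Not related. Possible never appears.
2. *Middle column.* Hold the alternative at merely possible and improve the timing from not clear to clear. The event moves from Possible to no category. Stronger temporal evidence removes the only intermediate answer.
3. *Right column.* With evidence of an alternative, clear timing gives Not related only, while unclear timing also satisfies Possible. The event with the weaker time link is the one that can still be attributed to the drug.
4. *Middle row, left.* Unclear timing with no alternative cause has no category either.

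**Sensitivity to one reading.** The table treats not clear and none as separate levels. If not clear were read to include none, the bottom row's middle and right cells would also satisfy Possible. The count would become Definite 1, Possible only 1, Not related only 4 − 2 = 2, two categories 1 + 2 = 3, no category 2; again 9. Overlap gets worse and the top row does not change.

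**Where the category is used.** Recording and SAE reporting (8.4) and the AE incidence and severity summary (11.2.2.3) do not depend on it. Nor do dose modification for severe AEs (5.3) or discontinuation for allergy symptoms (11.1), which do not refer to 8.3. It does determine the relatedness entry on the SAE form (8.4), and it bears on treatment-related death (9.2).

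**The case against.** The strongest reply is that little in the plan turns on relatedness. All AEs and SAEs are captured, every SAE is reported promptly, and the planned safety summary is all-cause. Section 9.2 sets no numerical threshold, does not refer to 8.3, and also lists repetition of SAEs, which is not limited to related events; repeated fatal events could support termination whatever their causality code. The primary endpoint and sample size are untouched. All of this stands, and it limits the size of the point.

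A second reply is that investigators will use clinical judgement and not apply the wording literally. That may happen, but the section offers no category for the cases where judgement is needed, so two investigators could code the same event differently and both follow the protocol.

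Three stronger readings are tempting and should be resisted.

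- *A reader might infer that merely taking another drug, or being ill after transplant, makes an event Not related.* The text requires evidence of an alternative cause. Concurrent medication or illness is only an example of such a cause, and routine supportive therapy alone does not meet the condition.
- *A reader might infer that any event with clear timing and a competing explanation falls to Not related.* It does so only when there is evidence for the alternative. When the alternative is merely possible, the event has no category. That is a defect, but a different one.
- *A reader might infer that nearly all drug reactions would be coded unrelated, or that a reported treatment-related AE rate would be pushed towards zero.* The protocol gives no share of events with an evidenced alternative cause, *Possible* remains open for unclear timing, and no treatment-related AE rate is stated as a planned output.

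**Conclusion.** The point holds. The categories in 8.3 are neither exhaustive nor mutually exclusive, and they treat clear timing perversely. Of nine combinations, two have no category and one has two. Clear timing can never lead to *Possible* and is overridden by evidence of another cause. The direction of the bias is away from the study drug, for events with a competing cause.

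Its size in events cannot be stated. The share of events with an evidenced alternative could be assumed anywhere from 0 to 100%, and the documents do not narrow that. It is reasonable to expect competing causes in post-transplant patients on supportive therapy, but this is a judgement about the population and not a figure in the protocol.

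The consequence is confined to relatedness coding, the causality entry on the SAE form, and one of several termination reasons in 9.2. This is worth correcting in a single-arm study with safety in its primary objective, but it does not threaten the all-cause safety results or the efficacy analysis, so it ranks below must-fix. The conclusion rests on reading and/or in its ordinary sense and on taking the three definitions as the complete scale.

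**What to change.** Reword 8.3 so that each event has exactly one place:

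- *Definite*: keep as it stands.
- *Possible*: a clear or reasonable temporal relationship even where other causes exist, or unclear timing where the drug cannot be excluded.
- *Not related*: no plausible temporal relationship, or an established other cause that makes a contribution from the drug implausible. Remove the and/or.

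State in 9.2 that treatment-related means *Definite* plus *Possible* as defined in 8.3. No change to AE recording, SAE reporting or the all-cause summary is needed.

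The cost is three definitions to review, one sentence in 9.2 and the wording of one CRF field, plus ethics committee approval of the revised protocol under 13.3. Relatedness counts may look less favourable. If causality has already been assigned for some events, those would need to be reassessed under the new wording, so the change is cheapest before that begins.

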## 8.4 Recording and Reporting of AEs and SAEs

All AEs and SAEs must be recorded in the appropriate CRF, regardless of whether they are causally related to the study treatment. Each SAE must be reported promptly on the Serious Adverse Event Report Form and submitted to the Independent Ethics Committee within 24 hours by the investigator. The information recorded on the Serious Adverse Event Report Form will include at least the following: subject number, identity of the event, study drug name and dose, investigator's assessment of the event's severity and relationship to study treatment, and investigator's name and signature. When examining original medical records, clinical monitors must collect and verify detailed information on AEs and SAEs. All AEs and SAEs should be followed up until they are resolved.

# 9. Rules of Withdrawal

## 9.1. Subjects Withdraw from the Study

Subjects can withdraw from the study at any time for any reason without affecting the investigator’s right to treat the disease. Given the interest of the subjects, the investigator has the right to request that the subjects withdraw from the study for any reason, including concomitant disease, AEs or treatment failure. The core group of clinical studies reserves the right to request that subjects withdraw from the study for deviation(s) from the protocol, administrative reasons, or other effective or ethical reasons.

The last assessment for subjects must be performed and documented in the CRF regardless of the time and reason for withdrawal. The reason for withdrawal from study participation must be documented in the CRF. All documents related to subjects should be completed. Despite withdrawal from the study, those subjects should be followed up and documented about their diseases until withdrawal of informed consent.

For subjects who withdraw from the study due to concomitant diseases or AEs, the details must be documented in the CRF with other appropriate and valuable data attached.

## 9.2. Premature Termination of the Study

Reasons for premature termination of the study include external events, repetition of SAEs, an increasing incidence of treatment-related death and slow study enrolment. All the subjects will be informed of the premature termination of the study via written consent. Any subject who decides to discontinue participation in the study must report to the principal investigator.

# 10. Rules of Follow-Up

## 10.1 Follow-up Period

Starting from the signing of the informed consent form.

## 10.2 Visit Scheduling

Every 7 days until the study is completed.

## 10.3 Contents

The contents of every follow-up visit will include subject’s complaints, vital signs, physical examination, clinical symptoms and clinical laboratory evaluations (haematology, serum chemistry, urinalysis, electrocardiogram, chest imaging examination, and BM assessment). All of the results must be documented in the original medical records.

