## 5.4 Follow-up

From the beginning of the first administration, the complete blood count will be monitored every 7 days within 20 days.

All the subjects will be followed for safety and tolerability within 20 days after luspatercept treatment. With the exception of haematologic AEs, all AEs will be graded according to the National Cancer Institute Common Toxicity Criteria version 5.0.

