## 6.4 Schedule and Methods of Efficacy Assessments

The patient's peripheral blood will be drawn to assess the recovery of WBC, ANC, Hb and platelets after the administration of luspatercept.

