### 7.2 Vital Signs and Physical Examination

Vital signs and physical examination results must be documented before randomization, once a week after enrolment. The next 8 steps must be performed:

⚫ Physical examination

⚫ Heart rate

⚫ Blood pressure

⚫ Body temperature

⚫ Rate of respiration

⚫ Body weight

⚫ ECOG performance status

⚫ Signs of infection

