### 7.4 Clinical Laboratory Evaluations

Before initiation of the study, the monitors will document the normal range of each test in every involved laboratory. During the study, the following steps will be performed:

⚫ Routine blood: white cell counts, neutrophil cell counts, hemoglobin, and platelet counts

⚫ Hepatic function: total bilirubin (both direct bilirubin and indirect bilirubin must be documented when total bilirubin is elevated), ALT, AST, lactic dehydrogenase, alkaline phosphatase, albumin and total protein

- Renal function: serum creatinine, urea nitrogen and uric acid
- Other biochemical indicators: amylase and lipase
- Electrolytes: sodium, potassium, calcium and magnesium
- Coagulation function: prothrombin time, prothrombin time-international normalized ratio, activated partial thromboplastin time and fibrinogen
- Urinalysis: protein, glucose and erythrocyte
- Electrocardiogram
- Chest imaging examination

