### 11.2.2.2 Analysis of Efficacy

The definitions of the efficacy endpoints have been described in detail in the previous section.

The efficacy endpoints will be hematologic improvement-erythroid, hematologic improvement-leukocyte and hematologic improvement-platelet. GraphPad Prism 10 (GraphPad Software, Inc., La Jolla, CA) will be used for the statistical analyses. The Mann‒Whitney U test will be used for continuous variables, and paired t tests will be performed to analyse the matched or paired data. *P* values <0.05 will be considered to indicate statistical significance.

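### Sections 10.2 and 10.3 together put an undefined BM assessment in every 7-day visit, at least 2 post-baseline per patient within 20 days, while Section 7.4 omits it

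*Protocol*

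**What the plan says.** Protocol Section 10.3 opens with "The contents of every follow-up visit will include" and closes its bracket of laboratory items with "urinalysis, electrocardiogram, chest imaging examination, and BM assessment". Nothing limits the marrow item to certain visits or to clinical need. Section 10.2 gives the frequency: "Every 7 days until the study is completed". Section 10.1 starts follow-up at signature of consent.

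Section 7.4 carries the same title as the group of tests in which 10.3 places the marrow item. It introduces its list with "During the study, the following steps will be performed" and names blood count, chemistry, coagulation, urinalysis, electrocardiogram and chest imaging. It does not name BM assessment and gives no frequencies.

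Section 5.1 requires a BM assessment at screening. Section 2.2 names the bone marrow microenvironment as a secondary objective, and the synopsis calls it exploratory. No section says whether BM assessment means an aspirate, a biopsy or something else.

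**The concern.** Staff who follow 10.3 would do a marrow assessment at each weekly visit. Staff who follow 7.4 would do none after screening. Visit content belongs in the protocol, so this is a rule the document states, not a detail left for an analysis plan.

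Patient burden is at stake. The participants have poor hematopoietic reconstitution after transplant. If the assessment is invasive, weekly repetition is a real load, and the efficacy evaluation does not need it. Section 6.4 says "peripheral blood will be drawn to assess the recovery of WBC, ANC, Hb and platelets". Section 11.2.2.2 says "The efficacy endpoints will be hematologic improvement-erythroid, hematologic improvement-leukocyte and hematologic improvement-platelet", and none of these is defined on marrow. There is also a conduct problem: if weekly marrow was never intended, each visit without it departs from 10.3 as written.

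**Working it through.** The protocol states no number of marrow assessments, so there is no figure of its own to reproduce. The planned 64 patients are used only as a multiplier.

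**Inputs**
- Visit interval: 7 days (10.2).
- Observation window: 20 days from first dose (5.4: "From the beginning of the first administration, the complete blood count will be monitored every 7 days within 20 days").
- Start of follow-up: consent (10.1).
- Planned enrolment 64, with 10% expulsion (11.1.1).
- One marrow assessment at screening (5.1).

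**Step 1. Per patient, counting from first dose.** floor(20 / 7) = 2. The visits fall on days 7 and 14; day 21 is outside the window. With screening the count is 2 + 1 = 3.

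**Step 2. Over the trial.** If all 64 complete: 2 × 64 = 128. Expulsion: 0.10 × 64 = 6.4, about 6, leaving 64 − 6 = 58. If those 6 contribute none: 2 × 58 = 116. Partial contributions fall in between, so the range is 116 to 128.

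**Step 3. Counting from consent.** Section 5.4 sets the clock for blood counts, whereas Section 10 starts at consent. Suppose consent is k days before first dose (k is an assumption). Visits then fall on days 7 − k, 14 − k and 21 − k after dosing.

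| k | Visit days within 20 days of first dose | Count |
| --- | --- | --- |
| 0 | 7, 14 | 2 |
| 1 | 6, 13, 20 | 3 |
| 2 | 5, 12, 19 | 3 |
| 3 | 4, 11, 18 | 3 |

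Three per patient gives 3 × 58 = 174 to 3 × 64 = 192. The choice of clock moves the days, but the minimum stays at 2.

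**Step 4. Visits past day 20.** The end point in 10.2 is open, and 5.4 runs safety follow-up for 20 days after treatment, not after first dose. Each further 7-day visit adds 1 per patient, or 58 to 64 in all.

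**Step 5. One named post-baseline assessment instead.** 1 × 58 = 58 to 1 × 64 = 64. The saving against Step 1 is 2 − 1 = 1 per patient, or 116 − 58 = 58 to 128 − 64 = 64. Against Step 3 it is 3 − 1 = 2 per patient.

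**Step 6. The sections that bear on on-study marrow**

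| Section | On-study marrow |
| --- | --- |
| 10.3 with 10.2 | At every 7-day visit, no qualifier |
| 7.4 | Not listed |
| 2.2 and synopsis | Marrow objective, no time points |
| 6.2, 6.3, 11.2.2.2 | No endpoint based on marrow |

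**The case against.** **The term is undefined.** The counts are counts of visits at which a BM assessment is due. They become counts of invasive procedures only if the assessment is an aspirate or biopsy. This stands, and the burden argument depends on that assumption.

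**Several sections show little by their silence.** A reader might infer that 5.4, 6.4, 7.2 and 11.2.2.2 all contradict 10.3. They do not. Section 7.2 covers vital signs and examination and omits blood tests too. Section 5.4 schedules the blood count without excluding other tests. Sections 6.4 and 11.2.2.2 deal with efficacy, and many safety tests feed no efficacy endpoint. Only 7.4 is a relevant mismatch. Even there the list does not claim to be complete, so the two sections could be read as complementary. That reading makes the gap an omission from one list, but it leaves weekly marrow in force through 10.3.

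**Marrow has a purpose here.** A reader might infer that post-baseline marrow serves nothing in this trial. The documents do not support that. The microenvironment objective justifies some post-baseline sampling. Section 11.1 stops the drug on relapse, for which marrow is a plausible though unstated use. The variables for the objective may be in an analysis plan that is not shown, and their absence is not criticised here. What the objective does not state is a weekly series. A single post-baseline sample paired with the screening one still gives a before-after comparison. If a time course is wanted, the protocol should name the days.

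**Conclusion.** The point holds as a minor matter of burden and consistency. As written, 10.3 with 10.2 requires BM assessment at every 7-day visit: at least 2 post-baseline per patient within 20 days of first dose (116 to 128 in all), 3 if visits are counted from a consent 1 to 3 days earlier, and more if visits continue past day 20. Section 7.4 does not list it. The conclusion that this over-samples fragile patients rests on the assumption of an aspirate or biopsy.

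Two stronger readings should be resisted. A reader might take the open end point in 10.2 together with the synopsis's 3-year duration to mean years of weekly marrow. The 3 years describe the study, not one patient's follow-up, and the only per-patient windows stated are of 20 days. A reader might also suppose that the efficacy result is compromised. Sample size, power, type I error and the primary endpoint do not depend on marrow and are unaffected.

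**What to change.** Remove BM assessment from the every-visit list in 10.3. Put one sentence, identical, in 7.4 and 10.3, for example: *BM assessment is performed at screening, once at the day-14 visit after first administration, and when clinically indicated (for example, suspected relapse).* The end of the 20-day window is an alternative to day 14, but it needs one visit off the 7-day grid. Naming a day counted from first dose avoids any doubt about what counts as after treatment if dosing is repeated.

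Also state what the assessment consists of. If serial marrow is needed for the microenvironment objective, list those days in place of the every-visit rule. The weekly visits, the electrocardiogram and chest imaging schedule, and the safety window can stay as they are.

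The cost is a short amendment to two sections with ethics committee approval, and the loss of intermediate marrow data for a secondary or exploratory objective. No listed efficacy endpoint loses data. Routine weekly marrow is the only safety observation given up.
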